## Methods: participants, interventions, and outcomes

### Study setting {9}

This multicentre research study takes place in four different clinical health care settings for youth in the Netherlands: Child and Youth Trauma Centre Kenter Jeugdhulp, GGZ Rivierduinen, UMC Utrecht, and Arq.

### Eligibility criteria {10}

Children are eligible to participate in the study if they meet the following inclusion criteria: (a) the child has been exposed to family violence; (b) the acute safety in the family has been established; (c) the child is between 12 and 20 years old; (d) the child lives at home with its caregiver(s); (e) caregivers, living with the child can participate in the systemic components; (f) the child has posttraumatic stress symptoms, at least intrusions and avoidance; and (g) caregivers and children master the Dutch language. The exclusion criteria for participating in the study are (a) children and caregivers who have acute psychotic symptoms or severe alcohol and drug addictions and (b) children with a suicide attempt in the past 3 months. The in- and exclusion criteria are established with an intake interview with a trained therapist and standardized questionnaires.

All therapists participating in the study are trained in the overall treatment program and have additional training in the part of the treatment program they will perform. Exposure therapy will be performed by therapists who have basic training in cognitive behavioural therapy. EMDR therapy will be performed by the therapists who completed the advanced EMDR training (VEN, Dutch EMDR Association). The bodily oriented therapy is offered by psychomotor therapists or therapists with experience in trauma and bodily oriented therapy under the supervision of an experienced psychomotor therapist. Parent therapy is performed by a family therapist or family worker. Together with a child therapist, the family therapist/worker will also offer the family sessions.

### Who will take informed consent? {26a}

Children between the age of 12 and 20 years old and referred to one of the participating trauma centres after being exposed to family violence will be given a brochure about the study, so are their parents. Subsequently, the therapist asks the family permission to share their contact details with the researcher. After approval, the therapist will send the researcher the contact details by email. Within two working days, the researcher will contact the family members separately to explain the study. An information letter with detailed information about the study will be sent to the families before the first intake interview at the respective centre. The families will have at least 1 week to consider their decision about participating in the study. If the family agrees to participate, informed consent will be sought from both parents, and children during the first intake. After the inclusion criteria are met and informed consent is obtained, participating families will be randomly assigned to one of the treatment conditions by an independent researcher using a computerized randomization procedure with lottery drawings.

### Additional consent provisions for collection and use of participant data and biological specimens {26b}

Participants will be informed that if they withdraw from the trial, their previously collected data will be used for the study. In the consent form, participants will be asked permission for the insight into their data, when relevant, by other people from the research team and regulatory authorities that are mentioned in the information letter. Participants will also be asked if the research team may contact them for future studies. The trial does not involve the collection of biological specimens.

### Interventions

#### Explanation for the choice of comparators {6b}

Intensive trauma therapy (ITT) is the comparator of family-based intensive trauma treatment (FITT) to examine the addition of a component with parenting therapy and family sessions to an intensive trauma-focused therapy component. It is important to understand if this addition is more effective in reducing trauma symptoms, improving parenting functioning, and increasing emotional and physical security in children, through the improvement of parent-child relationships—and thereby establishing long-term effects on the reduction of trauma symptoms and continuation of security in the family.

The second comparator for FITT is treatment as usual (TAU) to examine the addition of an intensive component to a low-frequent trauma-focused therapy with parenting therapy and family sessions. This comparator examines if FITT is as effective as TAU at the end of treatment and if FITT results in faster symptom reduction. In the view of adolescence as a critical period for development and peer influence [51], this faster symptom reduction is of great importance.

#### Intervention description {11a}

##### Components of ITT

ITT is a 3-week intensive trauma treatment program and contains a preparation phase in week 1 and an intensive phase in weeks 2 and 3.

#### Preparation phase: psycho-education and clustering

The preparation phase consists of two treatment days. On the first treatment day, the adolescent receives a 90-min online and interactive session of psycho-education about the impact of trauma and the treatment program. The aim is to inform the adolescent about (the consequences of) family violence, trauma and PTS disorder, stress regulation, the window of tolerance, and the treatment program. On the second treatment day, the adolescent is offered a 90-min session in which the different traumatic events are clustered. The adolescent and the therapist choose the six most traumatic memories, ordered by the degree to which they cause flashbacks, nightmares, and avoidance behaviour and elicit the most tension. These traumatic events will be the focus of the exposure and EMDR sessions.

#### Intensive phase: exposure, EMDR, and bodily oriented therapy

In the intensive phase, the adolescent has three treatment days per week. Each treatment day has a fixed program consisting of the following:
90-min Exposure60-min bodily oriented therapy90-min EMDR

##### Exposure

The exposure and EMDR in the program will be given by different therapists. One traumatic memory each day will be treated with exposure and EMDR. The exposure therapy is based on the Dutch translation [52, 53] of Foa’s prolonged exposure protocol [54]. Prolonged exposure therapy is a form of cognitive behavioural therapy in which the adolescent repeatedly describes the traumatic event in detail and present tense, focusing on the anxiety-provoking parts of the traumatic event. Every 5 to 10 min, the therapist checks the level of disturbance experienced by the adolescent. The adolescent learns fearful expectations stay away when being exposed to the trauma, and there is no need for avoidance behaviour.

##### Bodily oriented therapy

Between the sessions, exposure and EMDR individual bodily oriented therapy are offered by psychomotor therapists or therapists with experience in trauma and bodily oriented therapy under the supervision of an experienced psychomotor therapist. Through physical activities, the therapist supports the adolescent to:
Enhance the understanding of the association between the body and brainEnhance the understanding of the association between trauma and the bodyImprove stress-regulation skillsRecognize the effects of trauma on the bodyCalm the brain and body to prepare for the EMDR session

The therapist will work with bodily oriented exercises to achieve these goals.

##### EMDR

For the EMDR session, the most recent Dutch EMDR protocol for children and youth will be used, and all therapists completed the basic and advanced EMDR training of the Dutch EMDR Association. During EMDR therapy, the adolescent is asked to focus on the most disturbing image of the traumatic memory, and the therapist asks questions about the thoughts and feelings associated with the traumatic image and the level of disturbance. The therapist will ask the adolescent to focus on the image and the associated thoughts and feelings and at the same time focus on a distracting stimulus. This will bring a stream of associations in the form of thoughts, feelings, images, and bodily sensations and helps to reprocess the traumatic memory. The therapist will then ask what the adolescent notices and repeat the distracting stimulus. After a while, the adolescent will notice the level of disturbance will lower until the traumatic memory is desensitized. If necessary, the therapist can add cognitive interweaves during the desensitization phase to elicit new associations. An overview of ITT is presented in Table 1.

**Table 1 Tab1:** Overview of the intensive trauma treatment

Intensive trauma treatment (ITT)		
	Intervention	Adolescent
Week 1: preparation phase	Psycho-education	X
	Clustering	X
Week 2: intensive phase	Exposure	X
	Bodily oriented therapy	X
	EMDR	X

#### Additions in the preparation phase

##### Psycho-education for family and network

In FITT, the session psycho-education is together with the parents and the support system. This is a 90-min online and interactive session of psycho-education about the impact of trauma and the treatment program. The aim is to inform the adolescent and family system about (the consequences of) family violence, trauma and PTS disorder, stress regulation, the window of tolerance, trauma-sensitive parenting, and resilience and the treatment program.

#### Additions in the intensive phase

##### Parent therapy

In the intensive phase in weeks 2 and 3, parents receive three 60-min sessions of individual parent therapy per week from one family therapist or family worker. In dialogue, different topics are discussed: parental stress, support system, trauma-sensitive parenting, and traumas within the family. The parent therapy and EMDR take place simultaneously, and after these sessions, there is a short parent-child interaction moment where the adolescents share their thoughts and feelings on which the parents can practice supportive and trauma-sensitive parenting. The aim of the parent therapy is to:
Lower levels of parental stressIncrease parental supportIncrease knowledge about trauma-sensitive parenting and increase trauma-sensitive parenting skillsIncrease the insight that the family has a joint family story in which the different family members have their own memories and meaning about the traumatic events.

#### Additional integration phase

#### Family therapy

The integration phase consists of three 90-min sessions of family therapy. Two therapists support the family to talk about the experienced family violence and current conflicts. The goal of family therapy is to:
Create a shared trauma narrativeRecognize destructive communicative patternsRecognize emotional individual vulnerabilities and survival behaviour and their mutual effects in family relationshipsImprove skills to prevent escalations and cope with destructive patterns

In Table 2, an overview of FITT is presented.

**Table 2 Tab2:** Overview of the family-based intensive trauma treatment

Family-based intensive trauma treatment (FITT)					
	Intervention	Adolescent	Parents	Family	Network
Week 1: preparation phase	Psycho-education	X	X	X	X
	Clustering	X			
Weeks 2 and 3: intensive phase	Exposure	X			
	Bodily oriented therapy	X			
	EMDR	X			
	Parent therapy		X		
Week 4: integration phase	Family therapy	X	X	X	

##### Components of TAU

TAU is comparable across the four trauma centres and consists of low-frequent trauma-focused therapy with parenting therapy and family sessions. In contrast to the high intensity of FITT, TAU is offered about once a week and without therapist rotation. In TAU, the adolescents receive therapy from one therapist and parents receive therapy from another therapist. This individual or group-based trauma-focused cognitive behavioural therapy for adolescents and their parents is focused on the following components:
Psycho-education trauma and PTSD: increasing knowledge about (the consequences of) trauma and family violence and trauma-sensitive parenting and understanding the window of toleranceAffect regulation and coping: learning children to recognize and regulate feelings of stress and enhancing coping skillsTrauma processing: EMDR, exposure, writing therapy, or bodily oriented therapyParenting skills and competence: enhancing trauma-sensitive parenting skills, lowering levels of parental stress, and increasing social support.On indication: family relationships—sharing the trauma narrative and accompanying feelings and cognitions (for example feelings of shame or guilt) and strengthening of skills to prevent escalations

#### Criteria for discontinuing or modifying allocated interventions {11b}

In accordance with the Medical Research Involving Human Subjects Act, the sponsor will suspend the study if there is plausible ground that the continuation of the study will jeopardise the subject’s health or safety. The sponsor will then notify the accredited Medical Ethical Committee (from Amsterdam UMC) without undue delay of a temporary halt including the reason for such an action. The study will be suspended pending a further positive decision by the accredited Medical Ethical Committee. The investigator will take care that all subjects are kept informed.

#### Strategies to improve adherence to interventions {11c}

To increase treatment fidelity, a training protocol for (F)ITT is developed, and the therapists receive training in the (F)ITT protocol before data collection. Furthermore, therapists receive supervision on exposure, EMDR, parent and family therapy, and bodily oriented therapy during data collection. Exposure supervision is given by a healthcare psychologist who is a licensed supervisor from the Dutch cognitive-behavioural therapy association. EMDR supervision is given by healthcare and clinical psychologist who both are licensed supervisors from the Dutch EMDR association. The supervisor for the parent and family sessions is a clinical psychologist with advanced experience in the field of trauma and family therapy. The supervisor for the bodily oriented therapy is an experienced psychomotor therapist who works with traumatized children. To monitor adherence to the treatment protocol, therapists are asked to fill in a treatment evaluation form after each therapy session.

The trial will be monitored by the independent physician of the four participating youth mental health centres. Two times per year, the independent physician will randomly check the research file of a study participant on the following:
The involvement of a therapist registered in the Dutch register for healthcare professionalsThe presence of a safety plan in cases of suicidal thoughts/ideations and/or self-damaging behaviourThe compliance of in- and exclusion criteria (in the first year, the first three study participants will be checked, and thereafter, every half year, a participant will be randomly checked on in and exclusion criteria)Serious adverse events (SAEs) and if these are reported to the independent physician, inspection for healthcare and youth, the research institute and the Medical Ethical CommitteeThe presence of the cause conceptualisation

If any errors are observed, the files of all study participants within the specific centre will be checked.

To monitor the collection, storage, and processing of the data, each year, peer auditors trained in data management will randomly check the research file on the following:
Presence of informed consentsInclusion pace and drop out percentagePresence and completeness of the research data

If any errors are observed, the files of all study participants within the specific centre will be checked.

Furthermore, daily monitoring of the study will be done by the coordinating investigator, project leader, and principal investigator. Frequent contacts with the four trauma centres and research team meetings will be held to evaluate the progress of the study. All participating trauma centres have a contact person, who will be involved in all phases of the research.

#### Relevant concomitant care permitted or prohibited during the trial {11d}

Other psychological care for the adolescent will be paused from the first measurement until follow-up. Ongoing practical support can be continued. In cases of new warning signals of unsafety or suicidal thoughts, crisis interventions are offered by the involved centre participating in this study

#### Provisions for post-trial care {30}

After the follow-up measurement, an evaluation with the family will take place according to the procedure of the participating centres. If needed, post-trial care will be offered.

### Outcomes {12}

Table 3 presents an overview of the time points for each outcome measurement.

**Table 3 Tab3:** Measures

	*Measures*				Measurement			
	Measure	Items	Respondent*	Type	T(0)	T(1–11)	T(12/14)	T(13)
Child PTSD	CAPS-CA		c	Interview	*			*
	CRIES	13	cp	Questionnaire	*	*	*	*
	TSCC	54	c	Questionnaire	*		*	*
Child functioning	SDQ	25	cp	Questionnaire	*		*	*
	CDI	28	c	Questionnaire	*		*	*
	CDC	20	p	Questionnaire	*		*	*
Parent functioning	NOSI-K	25	p	Questionnaire	*	*	*	*
	Trauma-informed	6	p	Questionnaire	*		*	*
	IES-r	22	p	Questionnaire	*		*	*
	YAS-R	29	p	Questionnaire	*		*	*
	DPAS	9	p	Questionnaire	*		*	*
Structural emotional and physical safety	CTS	77	p	Questionnaire	*		*	*
	CTS-pc	27+39	c	Questionnaire	*		*	*
	PRTI	21	p	Questionnaire	*		*	*
	ACE-Q	10	p	Questionnaire	*		*	*
	New IPV incidents	8	cp	Questionnaire	*	*	*	*
	SIS	43	c	Questionnaire	*		*	*
	SIFS	7	c	Questionnaire	*		*	*
	SIM-PR	28	p	Questionnaire	*		*	*
	Security scales	15	cp	Questionnaire	*		*	*
	FIT	4 tasks	cp	Observation			*	
Total items child					232	21	232	232
Total items parent					335	46	335	335

Marked measures are part of routine outcome measuring

#### Primary outcomes

##### Child PTSD symptoms

The Clinician-Administered-Ptsd-Scale-Children-And-Adolescents (CAPS-CA) [55] is a standardized clinical interview, to assess PTSD conform the DSM-5 standards. A Dutch translation of the CAPS-CA [56] is administered to children aged 8–18. The core traumatic event is chosen based on the life events checklist. If the core traumatic event is a sequence of events, which is often the case in family violence, a brief term is chosen to capture the core of these events. The CAPS-CA assesses the frequency and intensity in which each PTS disorder symptoms occur. A 5-point severity rating scale is used for all symptoms, ranging from 0 (= absent) to 4 (= extreme/incapacitating). An example item is *In the past month, have you had upsetting thoughts, pictures or sounds of what happened come into your mind when you didn’t want them to?*. A total symptom severity score is calculated by summing the severity scores for items 1–20. A total symptom score can also be calculated per cluster; re-experiencing (items 1–5), avoidance (items 6 and 7), negative alterations in cognitions and mood (items 8–17), and hyperarousal (items 15–20). A symptom cluster score may also be calculated for dissociation by summing items 29 and 30. To determine the PTSD diagnostic status, individual symptoms should be dichotomized as “present” or “absent”. A symptom is considered present only if the corresponding item severity score is rated 2 (= moderate/threshold or higher). Items 9 and 11–20 have the additional requirement of a trauma-relatedness rating of definite or probable. The DSM-5 diagnostic rule requires the presence of at least one criterion B symptom, one criterion C symptom, two criterion D symptoms, and two criterion E symptoms. Also, criteria F (disturbance at least 1 month) and G (disturbance that causes either clinically significant distress or functional impairment) must be met. Reliability of the CAPS-CA in a Dutch sample for the total scale ranged from coefficient *a* of 0.77 to .86, and the interrater reliability of the total scale is 0.99. Caps-CA also demonstrated divergent, convergent, and discriminant validity [57].

The Children’s Revised Impact of Event Scale [58] is translated in Dutch [59] and is a questionnaire for the assessment of traumatic impact across different types of trauma and life-threatening events. Children and parents will rate 13 items according to the frequency of their occurrence in the past 24 h in relation to the traumatic experiences (1 = none, 2 = rarely, 3 = sometimes, and 4 = often). Example items are: “Do you think about the ……. even when you don’t mean to?”, and “Do you avoid talking about …?” The sum score is used as an indicator of traumatic impact (ranging from 0 to 65). A score of 30 and over has been suggested as the most efficient cut-off for discriminating heightened risk for PTSD. Within a semi-clinical study population, Cronbach’s *a* was .89 for the 13-items child version [60].

The Trauma Symptom Checklist for Children [61], Dutch translation: *Trauma Symptoom Controle Lijst voor* Kinderen [62], is a questionnaire to assess the self-reported posttraumatic stress symptoms in children (8–12 years). It consists of 54 items clustering in eight scales: two validity scales (under response, hyper response) and six clinical scales (anxiety (9 items), depression (9 items), post-traumatic stress disorder (10 items), dissociation (10 items), anger (9 items), and sexual concerns (10 items)). A 4-point severity rating scale is used for all symptoms, ranging from 0 (= absent) to 3 (= very often). An example item is “feeling *afraid something bad might happen”.* Reliability was high for all subscales, with a Cronbach alpha ranging from 0.72 to 0.83 in a large sample [63].

##### Emotional security and physical safety

To assess the severity and intensity of the violence that children have been exposed to, a combined measure will be used including items from the Conflict Tactics Scale (78 items, 8-point rating scale) [64], the Conflict Tactics Scale parent child (27 and 39 items, 8-point rating scale) [64], the Parents Report of Traumatic Impact (21 items ) [65], and the Adverse Childhood Experience Questionnaire (10 items, 5-point rating scale) [66]. An example item is *I punched or hit my partner with something that could hurt*. This combined questionnaire has been used in a previous study on the effectiveness of a psycho-educational prevention program for children exposed to IPV [67]. The questionnaire covers the topics and duration of the violence and the nature of the arguments in the relationship with the (ex-partner), followed by items from the Conflict Tactics Scale parent child and Parents Report of Traumatic Impact about problems between parent and child, and traumatic events the child has experienced. The questionnaire also includes items about traumatic experiences in parents’ own childhood. A short questionnaire of 8 items for parent and child is added to assess if any new IPV incidents or other stressful events occurred.

To assess emotional security, the Dutch translation of the Security in the Interparental Subsystem [68] will be used. The Security in the Interparental Subsystem consists of 43-items with a 4-point ordinal scale (1 = not at all true of me, 4 = very true of me). Children are asked to answer questions about previous violence and conflicts between parents and current violence and conflicts between parents and partners. It has three scales and seven subscales: emotional reactivity (emotional reactivity (9 items), behavioural dysregulation (3 items), regulation of exposure to affect avoidance (7 items), involvement (6 items)) and internal representations (constructive family representations (4 items), destructive family representations (4 items), and conflict spillover representations (4 items)). An example item is *When my parents have an argument the family is still able to get along with each other*. The subscales show satisfactory internal consistency and test-retest reliability, and previous research supported the validity of the SIS scale [68]. Children will be asked to answer the same questions with respect to past fights and arguments between their parents and current fights and arguments between their mother and partner at T0, T12/14, and T13.

The Security in the Family System scale [69] will be used to assess how much children perceive their families as a reliable source of protection, stability, and support. The subscale “Secure” will be used, which assesses a secure pattern of emotional security. Children indicate the extent to which they agree with 7 statements using a 4-point scale ranging from “completely disagree” (1) to “completely agree” (4). An example item is *It’s worth caring about family members, even when things go wrong*. Psychometric properties of this security subscale are good, Cronbach’s *a* = 0.85 and test-retest reliability = 0.82 [69].

Caregivers report on children’s emotional security, including their emotional reactivity, behavioural involvement, and avoidance, after witnessing arguments between their parents using the Dutch translation of the Security in the Marital Subsystem Scale (SIMS) [68]. Items are completed on a 5-point ordinal scale from 1 (not at all like him/her) to 5 (a whole lot like him/her) and include feeling sad, angry, afraid, and upset (e.g. “Still seems upset after we argue”). The SIMS has been found reliable and has demonstrated discriminant, convergent, and predictive validity [70].

The Security Scale [71, 72] is a 15-item self-report questionnaire for children between the ages of 8 and 18 and measures self-reported attachment security with their parents [73]. Children and parents (independently) report on responsiveness and availability of the parent in the parent-child relationship (attachment). Each item is rated on a 5-point Likert scale (1 = strongly agree, 5 = strongly disagree). An example item is *I feel my mother really understands me*. Several studies indicate adequate reliability and validity [74]. High internal consistencies for 10 and 12-year-olds (*α* = 0.82, *α* = 0.79) are reported [75]. Test-retest reliability over a 2-week period was high (*r* = 0.75) [73]. The Security Scale is related to other attachment measures [75]. In a Dutch sample, internal consistency for the child version was *α* = 0.81 [76].

The Family Interaction Task (FIT) [77] is an observational instrument that measures parent-child interaction and consists of four tasks in which parent and child are instructed to complete a series of interactive tasks together. The FIT consists of four structured tasks: (1) guessing words by getting clues, (2) etch a sketch, (3) conflict task, and (4) completing a difficult but solvable puzzle by untangling a fixed ring from a standard within 4 min. These tasks are designed to elicit variations in parental and adolescent autonomy-promoting behaviours and emotional affect. The tasks are originally developed for children in middle childhood, but the tasks have been adapted for adolescents. Rating scales range from 1 to 5 and a higher score indicates a greater presence of that particular construct. Ratings are based on the complete session. Each videotaped session is independently coded by two coders (researchers). Interrater reliability was adequate (*n* = 101, ICC range .87–.94) in a Dutch sample [76].

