## Statistical methods

### Statistical methods for primary and secondary outcomes {20a}

The measurement level of each variable is at least ordinal. We control for the duration and severity of family violence [96], child functioning, parental psychopathology [97], and new incidents of family violence as a priori potential confounders. Analyses will be performed using the latest version of the software package Statistical Package for the Social Sciences (SPSS). First, to determine whether changes on continuous measures are different per treatment, we use linear mixed models. Continuous measures with only one time point will be analysed with independent samples *T*-test. Changes in categorical outcomes over the course of treatment across the conditions are tested with generalized estimating equations (GEE). To handle missing data, we will use maximum likelihood estimation within the linear mixed model analyses. For the planned GEE, we will explore the possibilities to deal with missing data, depending on the amount, randomness, and type of data missing. Analyses will primarily be performed according to the principles of intention-to-treat; however, they will be repeated as per-protocol analyses (see Table 4).

**Table 4 Tab4:** Statistical analyses

*Statistical analyses*					
	Measure	Type of data	Timepoints	Statistical analysis	Subjects
Child PTSD	CAPS-CA	Categorical	3	GEE	ITT/PP
	CRIES	Continuous	4	Mixed models	ITT/PP
	TSCC	Continuous	3	Mixed models	ITT/PP
Child functioning	SDQ	Continuous	3	Mixed models	ITT/PP
	CDI	Continuous	3	Mixed models	ITT/PP
	CDC	Continuous	3	Mixed models	ITT/PP
Parent functioning	NOSI-K	Continuous	4	Mixed models	ITT/PP
	Trauma-informed	Continuous	3	Mixed models	ITT/PP
	TSI	Continuous	3	Mixed models	ITT/PP
	YAS-R	Continuous	3	Mixed models	ITT/PP
	DPAS	Continuous	3	Mixed models	ITT/PP
Structural emotional and physical safety	CTS	Continuous	3	Mixed models	ITT/PP
	CTS-pc	Continuous	3	Mixed models	ITT/PP
	PRTI	Continuous	3	Mixed models	ITT/PP
	ACE-Q	Continuous	3	Mixed models	ITT/PP
	New IPV incidents	Continuous	4	Mixed models	ITT/PP
	SIS	Continuous	3	Mixed models	ITT/PP
	SIFS	Continuous	3	Mixed models	ITT/PP
	SIM-PR	Continuous	3	Mixed models	ITT/PP
	Security scales	Continuous	3	Mixed models	ITT/PP
	FIT	Categorical	1	Independent samples T-test	ITT/PP

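### CTS, CTS-pc and PRTI are described as exposure history but modelled as change outcomes, with no post-baseline window stated

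*Protocol article*

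**What the plan says.** Under Primary outcomes (Emotional security and physical safety), the protocol article combines items from the CTS, CTS-pc, PRTI and ACE-Q. The stated purpose is: "To assess the severity and intensity of the violence that children have been exposed to, a combined measure will be used". The block is said to cover the duration of the violence, the nature of arguments with the (ex-)partner, and "problems between parent and child, and traumatic events the child has experienced". New events are given to another form: "A short questionnaire of 8 items for parent and child is added to assess if any new IPV incidents or other stressful events occurred".

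No recall period is given for the block. Other instruments have one: past month in the CAPS-CA example item, 24 hours for the CRIES, two weeks for the CDI2 and the last week for the IES-R. The SIS asks about past and current conflict separately.

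The statistical section uses the same construct as an adjustment variable: "We control for the duration and severity of family violence". It later adds intensity and new IPV incidents to the covariates. It also says that, "to determine whether changes on continuous measures are different per treatment, we use linear mixed models". Table 3 schedules CTS (parent), CTS-pc (child) and PRTI (parent) at T0, T12/14 and T13. Table 4 has the row "CTS Continuous 3 Mixed models ITT/PP", where ITT means intention-to-treat, and identical rows for CTS-pc and PRTI. New IPV incidents has its own row, with four time points.

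**The concern.** The same scales are described as exposure history, belong to a construct that is adjusted for as a confounder, and are listed as primary-domain outcomes whose change is compared between arms. These uses fit together only if the repeated forms ask about a period that starts at or after T0, and the text does not say so. If they look further back, part of each post-treatment score is violence from before randomisation, which treatment cannot alter, and a true FITT-ITT difference in safety becomes harder to see.

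A second mechanism concerns who reports. FITT adds parent therapy that addresses traumas within the family, and family sessions in which "Two therapists support the family to talk about the experienced family violence and current conflicts". ITT has neither. Parents who complete the CTS and PRTI after FITT might report earlier violence more fully, which would shift the contrast against FITT.

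**Working it through.** **1. Reproduce the plan's sample size.** Inputs (Sample size section): f = 0.18, two groups, m = 2 measurements, correlation 0.5, ε = 1, two-sided 5%, power 80%. Noncentrality λ = f²·N·m/(1 − ρ), with 1 and N − 2 degrees of freedom. At N = 64, λ = 0.0324 × 64 × 2/0.5 = 8.294 and power is 0.809. At N = 62 power is 0.797. The stated 64 reproduces, as do 3 × 32 = 96 and 96/0.80 = 120.

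The same effect on the change score is d = 2 × 0.18 × √(2/0.5) = 0.72 SD of change (check: 64 × 0.72²/4 = 8.294). With 32 per arm, power is 0.81. This is taken as the benchmark for a score that covers only in-trial violence. That is an assumption, because the document gives no effect size specific to violence.

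**2. Window reaching back before T0.** Let t be the months since T0 and L the recall window. The share of the window that treatment can affect is min(1, t/L), and the effect becomes 0.72 × share. The SD of change is held at its design value. T12/14 is taken as t ≈ 1 and T13 as t ≈ 4 (4 weeks of FITT plus 3 months of follow-up). L is not in the document, so it is ranged.

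| Time | L (months) | Share | d | Power, 32 per arm |
|---|---|---|---|---|
| T12/14 | 1 | 1 | 0.72 | 0.81 |
| T12/14 | 4 | 0.25 | 0.18 | 0.11 |
| T12/14 | 12 | 0.083 | 0.06 | 0.06 |
| T13 | 4 or less | 1 | 0.72 | 0.81 |
| T13 | 6 | 0.667 | 0.48 | 0.47 |
| T13 | 12 | 0.333 | 0.24 | 0.16 |

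Holding the SD fixed matters. Where the windows of two visits overlap and the shared months are reported identically, those months cancel from the change, its SD shrinks too, and the loss is smaller than shown.

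**3. Cumulative score.** If the form covered everything to date, history reported identically at each visit would cancel and power would stay at 0.81. With re-report error, d = 0.72/√(1 + 2(1 − r)s²), where s is the SD of history relative to new violence and r is the reliability of re-reporting. Both are assumed.

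| s | r = 1 | r = 0.9 | r = 0.8 |
|---|---|---|---|
| 1 | 0.81 | 0.74 | 0.67 |
| 3 | 0.81 | 0.40 | 0.26 |
| 5 | 0.81 | 0.21 | 0.14 |

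Example for s = 3, r = 0.9: √(1 + 0.2 × 9) = √2.8 = 1.673, and 0.72/1.673 = 0.43.

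**4. Differential reporting.** Let the extra reporting in FITT be e SD of change. The net FITT-ITT difference is −0.72 + e, so e = 0.25 leaves −0.47, e = 0.72 cancels the benefit and e = 1.0 gives +0.28. Nothing in the document indicates the size of e.

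**The case against.** The strongest objection is that the document nowhere says these scales are scored over a lifetime. The phrasing about exposure would read the same at every visit, and item instructions are often left to the questionnaire or the full protocol. This stands against two inferences a reader might draw: that history must swamp new violence, and that the scores can fall only through reporting error. Both need a cumulative score. A rolling window lets scores fall when violence stops, and constant history cancels from a within-person change. It does not remove the conflict in the stated text, which gives new incidents to another form, adjusts for the violence history, and still lists the history scales as change outcomes.

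A reader might also infer that FITT's disclosure work reverses the sign. The documents do not show this. At the design effect, reversal needs extra reporting above 0.72 SD of change. In both arms adolescents receive psycho-education on family violence, select their six most traumatic memories and describe them in detail, so the child-reported CTS-pc gives little reason to expect a difference between arms. The mechanism is plausible for the parent-reported CTS and PRTI only. It is also specific to FITT versus ITT, because TAU has parent therapy too and may share the trauma narrative on indication.

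Nor does the physical-safety comparison rest on these three scales alone. New IPV incidents is already a separate outcome, and the primary question names structural emotional safety, which several other scales measure. Finally, acute safety must be established before entry, so in-trial violence may be rare and even a bounded score may not reach the benchmark power.

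The block has a related feature: "The questionnaire also includes items about traumatic experiences in parents’ own childhood". Such items cannot change with treatment, but they do not settle the window for the CTS, CTS-pc or PRTI.

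**Conclusion.** The concern holds as a conflict between the description of the three scales and their role in Table 4. Its cost is conditional. At T13 there is no loss if the repeated forms look back no further than T0. Power is about 0.47 with a 6-month window and 0.16 with a 12-month window, against 0.81. These figures assume 32 per arm, the design effect of 0.72 SD of change on in-trial violence, a T13 about 4 months after T0, and an unchanged SD of change. At T12/14, about 1 month after T0, any window of several months leaves little signal. Under a cumulative score the loss comes only from re-report error and ranges from none to severe. Reporting bias in favour of ITT on the CTS and PRTI is possible but unquantified. The sample size of 64 per comparison is not affected.

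**What to change.** Choose one of two routes and state it in the outcomes and analysis sections.

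- **Bounded repeat forms.** Limit CTS, CTS-pc and PRTI at T12/14 and T13 to events since the form was last completed. Analyse those bounded scores at the two post-baseline visits with the T0 history score as covariate, not as the first point of a change. Record the length of each window, because treatment lasts 3 weeks in ITT and 4 in FITT, and express scores per unit of time if the windows differ.
- **Baseline only.** Keep the three scales at T0 as the exposure covariate, delete their rows from Table 4, and let New IPV incidents carry the physical-safety outcome. In that model it must not also be a covariate.

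The first route costs one instruction line on the repeated forms and some plan wording. The second costs wording only, and fewer violence scales are then reported as outcomes. Neither needs extra families or visits. The first also reduces the room for differential reporting of old violence, since events before T0 are no longer asked about.
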